### Inclusion and Exclusion Criteria

#### Inclusion Criteria

Participants should meet the following criteria to be eligible to enroll in the study:

40-59 years of ageCurrent smokers who are smoking conventional cigarettes with a minimum of a ten pack-year smoking history (calculated by taking the average number of cigarettes smoked per day divided by 20 and multiplied by the number of years smoked):Asymptomatic current smokers: no symptoms (CAT<10, 6MWT≥450 meters) and preserved pulmonary function based on spirometry (FEV_1_/FVC of at least 0.70 after bronchodilation treatment and FVC ≥80% of the expected value) and respiratory symptoms (CAT ≥10); OR “Grey zone” current smokers: initially preserved pulmonary function based on spirometry, but with clinical symptoms based on CAT (>10) and 6MWT (<450); ORCurrent smokers with a confirmed diagnosis of COPD (Global Initiative for Chronic Obstructive Lung Disease [GOLD] stage I-III).Able to use and willing to be trained to use mHealth devices.Provide written, informed consent to participate in the study.

Participants will undergo the current standard of care based on their smoking disease states or lack of disease state.

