**Methods:**

A total of 3 cohorts, with 9 participants in each, will use mHealth devices for 90 days while undergoing the current standard of care. These groups are: 9 “non-COPD,” otherwise healthy, smokers; 9 “grey zone” smokers (forced expiratory volume in 1 second/ forced vital capacity ≥0.70 after bronchodilator treatment; COPD Assessment Test ≥10); and 9 smokers diagnosed with Stage 1-3 COPD. Rates of recruitment, retention, and adherence will be measured. Overall, two mHealth devices will be utilized in the study: the AnaMed Original Equipment Manufacturer device (measures distance, energy expenditure, heart rate, and heart rate variability) and the Air Next mobile spirometry device. The mHealth devices will be compared against industry standards. Additionally, a questionnaire will be administered to assess the participants’ perceptions of the mHealth technologies used.

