## Introduction

Chronic obstructive pulmonary disease (COPD) accounted for 3.2 million deaths globally in 2015 [1] and is the fourth leading cause of death both worldwide and in Kazakhstan [2]. COPD is a heterogeneous condition, with a variety of disease-related phenotypes [3,4], and its main risk factor is cigarette smoking [5]. The chronic airflow limitation that characterizes COPD is caused by obstructive bronchiolitis and parenchymal destruction (emphysema). Pulmonary emphysema is a form of COPD; however, pulmonary emphysema without airway obstruction is common in smokers [6,7]. Smokers with symptoms suggestive of COPD who do not qualify for a diagnosis of COPD based on spirometry are referred to as “grey zone” COPD patients. They have preserved pulmonary function (forced expired volume in 1 second/forced vital capacity [FEV_1_/FVC] of at least 0.70 after bronchodilator and FVC ≥80% of the expected value) and respiratory symptoms (COPD assessment test [CAT] ≥10).

Continuous monitoring is vital for the management of COPD. Implementing telemedicine and mobile health (mHealth) innovations has allowed clinicians to intervene in COPD earlier and prevent complications. However, there remain challenges in the form of alarm frequency and response, both of which need to be implemented into the existing workflow [8]. Data flow and workflow processes need to be designed with precision at the outset if telemedicine is to be applied in clinical practice. Telemonitoring using mHealth devices has the potential to promote self-management, improve control, increase quality of life, and prevent hospital admissions [9-13]. Technological advances in mHealth home telemonitoring (electronic health [eHealth]) programs and systems can affect care for patients with COPD [12,14-17]. mHealth devices are an emerging opportunity in clinical studies, and their utility (ie, sensitivity, accuracy, and reproducibility) has previously been assessed for telemonitoring for COPD [14].

Telemonitoring is a promising alternative or adjunct to the provision of traditional health care services in COPD [18]. Although some studies have shown that telemonitoring may improve some clinical outcomes and reduce health care costs [19,20], the effects of telehealth interventions on emergency department attendance, hospital admissions, duration of admissions, health-related quality of life, costs, and mortality remain less certain [18,21-25].

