## Methods

### Study Design

This is a proof-of-concept, open-label, three-arm, observational, single-center feasibility study. A total of 27 participants in three cohorts will use the mHealth devices for 90 days while undergoing the current standard of care based on their smoking disease state or lack of disease state. The groups are made up of nine “non-COPD,” otherwise healthy, smokers, nine “grey zone” smokers (ie, FEV_1_/FVC ≥0.70 after bronchodilator treatment, CAT ≥10; six-minute walk test [6MWT]<450 meters), and nine smokers diagnosed with Stage 1-3 COPD.

In each group, nine participants will be randomly assigned to three types of reminders: three participants will be reminded every morning by text message or phone call and contacted every evening by phone or chat services (eg, Skype, WhatsApp, Viber, texting) to share their experiences and feedback on mHealth device usage; three participants will receive only morning reminders; and three participants will receive neither morning reminders nor evening communication/feedback.

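### The asymptomatic inclusion criterion requires CAT below 10 and CAT of at least 10 in the same item, and the grey-zone CAT cut-off in the eligibility list differs from the one used elsewhere in the protocol.

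*Protocol article*

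**What the plan says.** The Inclusion Criteria list three alternative kinds of current smoker.

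- **Asymptomatic.** The item starts "Asymptomatic current smokers: no symptoms (CAT<10, 6MWT≥450 meters) and preserved pulmonary function based on spirometry". It then gives the spirometry limits (post-bronchodilator ratio of at least 0.70, FVC at least 80% of expected) and ends "and FVC ≥80% of the expected value) and respiratory symptoms (CAT ≥10". The word OR that introduces the next alternative comes only after that clause.
- **Grey zone.** Spirometry initially preserved, "but with clinical symptoms based on CAT (>10) and 6MWT (<450".
- **COPD.** A confirmed diagnosis, GOLD stage I to III, with no CAT limit.

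The grey zone is defined in three other places. The Abstract (Methods) has "COPD Assessment Test ≥10" and no walk-test limit. The Introduction has "respiratory symptoms (COPD assessment test [CAT] ≥10", also with no walk-test limit. Study Design has "CAT ≥10; six-minute walk test [6MWT]<450 meters". The Abstract and Study Design describe the first cohort as non-COPD and otherwise healthy. Each cohort has nine participants, who are randomised three each to three types of reminder.

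**The concern.** The Inclusion Criteria are the list that site staff would apply at screening, and CAT is one of the variables that places every smoker without COPD in a cohort. Two faults sit in that list: a criterion that cannot be met as worded, and a cut-off that disagrees with the study's own design section.

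Three things depend on the wording:

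- **Recruitment rate.** This is a primary measure, defined in Outcome Measures from the numbers screened and enrolled. A person with CAT 10 may be a screen failure under one section and enrolled under another.
- **Filling the cohorts.** Recruitment uses quota sampling, so the thresholds decide who may fill each set of nine places.
- **By-group results.** Statistical Analysis states that all analyses are also done by study group. With nine per cohort, one person in the wrong cohort is 1/9 = 11% of it, and one third of a reminder cell of three.

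**Working it through.** **1. The asymptomatic item.** Its parts are joined by *and*: CAT < 10, 6MWT ≥ 450 m, the spirometry limits, and CAT ≥ 10. The sets {CAT < 10} and {CAT ≥ 10} have no score in common, so the number of qualifying scores is 0. The cohort affected is 9/27 = 33% of the planned sample. The last clause, with the spirometry limits before it, closely matches the grey-zone definition in the Introduction, which suggests that text was carried over from there.

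**2. The boundary at CAT 10.** The table takes a smoker without COPD whose spirometry meets both limits, and shows the cohort under each section. The semicolon in the Study Design definition is read as *and*.

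| CAT | 6MWT | Inclusion Criteria, literal | Inclusion Criteria, stray clause removed | Grey zone under Study Design? | Grey zone under Abstract and Introduction? |
|---|---|---|---|---|---|
| 9 | ≥ 450 m | none | asymptomatic | no | no |
| 9 | < 450 m | none | none | no | no |
| 10 | ≥ 450 m | none | none | no | yes |
| 10 | < 450 m | none | none | yes | yes |
| 11 | ≥ 450 m | none | none | no | yes |
| 11 | < 450 m | grey zone | grey zone | yes | yes |

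At CAT 10 the Inclusion Criteria offer no non-COPD cohort at any walking distance. Study Design admits the same person to the grey zone when the distance is under 450 m. A smoker with confirmed GOLD I to III COPD and CAT 10 enters the COPD cohort in every case.

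**3. What aligning the cut-off alone would do.** If the stray clause is removed and the list also reads CAT ≥ 10, the row for CAT 10 with 6MWT < 450 m becomes grey zone. The row for CAT 10 with 6MWT ≥ 450 m stays empty. So do all non-COPD smokers with CAT ≥ 10 and 6MWT ≥ 450 m, and all with CAT < 10 and 6MWT < 450 m, because the list ties the two tests together.

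**4. The plan's precision figures.** Sample Size Calculation gives 13–47% for a recruitment rate of 30%, ±13% for retention with 15% dropout, and 17% for adherence of 70%. With half-width 1.96 × √(p(1 − p)/n) and n = 27:

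- recruitment: 1.96 × √(0.30 × 0.70/27) = 0.173, interval 12.7% to 47.3%
- retention: 1.96 × √(0.85 × 0.15/27) = 0.135
- adherence: 1.96 × √(0.70 × 0.30/27) = 0.173

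These agree with the stated figures. They use the pooled 27 and no CAT threshold, so the fault does not touch them.

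**The case against.** The strongest reply is that this is a visible drafting slip. The item is labelled asymptomatic, its first condition is absence of symptoms, and the Abstract and Study Design call the cohort otherwise healthy. A reader would discard the last clause. That stands: the intended meaning of the asymptomatic item is recoverable, and nothing in the article shows that anyone was wrongly screened out or placed in the wrong cohort. A reader might infer that a third of the sample cannot in practice be enrolled. The documents do not support that; 9 of 27 is the consequence of a literal reading, not a forecast.

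A second reply is that the boundary conflict concerns a single score in a small study whose group comparisons are largely descriptive, and which says itself that it cannot estimate effect size. That limits the damage but does not remove the conflict. The label does not tell staff whether CAT 10 is grey zone, and two sections answer differently.

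A third reply is that the Introduction is background and an abstract condenses, so their silence on the walk test proves little. That is fair. The conflict over the CAT cut-off nevertheless remains between Study Design and the Inclusion Criteria, both of which are operative text.

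**Conclusion.** The point holds as an eligibility list that is wrong as written and cheap to correct. The asymptomatic item contradicts itself. The grey-zone cut-off is above 10 in the Inclusion Criteria and at least 10 in the Abstract, Introduction and Study Design. The consequences fall on cohort assignment, by-group analyses and the recruitment rate. How many people they affect is unknown, because the article gives no distribution of CAT scores among those screened.

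Two further inferences should be resisted. It is not true that a CAT of 10 fits no cohort at all: that holds only for smokers without COPD and only under the Inclusion Criteria, since the COPD cohort has no CAT limit and the other sections place a score of 10 in the grey zone, subject in Study Design to the walk test. Nor would a common cut-off of 10 make the two non-COPD cohorts complementary, because the walk-test condition still leaves the discordant combinations unassigned.

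The conclusion assumes that the conditions within each item are joined by *and*, as the wording indicates, and that the full protocol, which is not shown, does not already carry a corrected list.

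**What to change.** 1. In the Inclusion Criteria, delete the closing symptom clause (CAT ≥ 10) from the asymptomatic item.
2. Reconcile the grey-zone CAT cut-off in that list with the one used in the Abstract, Introduction and Study Design, so that a score of 10 is treated in one way throughout.
3. Decide whether the six-minute walk test is part of the cohort definitions. It is in Study Design and the Inclusion Criteria, and absent from the Abstract and Introduction. If it stays, state that smokers without COPD whose CAT and walk test disagree are ineligible.
4. Inclusion began in June 2019, so check the cohort of everyone already enrolled against the single rule, using the CAT, walk test and spirometry that Table 1 schedules at screening. Report any discrepancy, and leave the randomised reminder allocation undisturbed.

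The cost is a short text correction and a check of at most 27 records, with no new data collection. If the check finds discrepancies, the 9/9/9 cohorts and the three-way reminder split within them may no longer be exact, and the report should say so.

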#### Exclusion Criteria

Participants meeting any of the following exclusion criteria are not eligible to enroll in the study:

Smokers with COPD exacerbation (defined as a change in symptoms requiring increased doses of current medicines or the prescription of new medicines, such as corticosteroids or antibiotics) that has not resolved at least 28 days before screening. Smokers with COPD exacerbations occurring after screening but before the first study visit should also be excluded.Smokers with pneumonia or other respiratory tract infections that have not resolved at least 14 days before screening. Any participant that experiences pneumonia occurring after screening but before the first study visit should also be excluded.Smokers with other active respiratory disorders: tuberculosis, lung cancer, significant bronchiectasis, sarcoidosis, bronchial asthma, lung fibrosis, pulmonary hypertension, interstitial lung diseases, or other active pulmonary diseases.Any comorbid medical condition that, in the opinion of the investigator, would make participation in the study unsafe or unfeasible. This includes conditions that prohibit completion of exercise testing, such as orthopedic, neurological, cardiovascular, or other conditions that significantly impair standard biomechanical movement patterns and limit the ability to walk/cycle, as judged by the investigator.Use of supplemental oxygen therapy.Inability to abstain from smoking during the period in which the participant is admitted to the Kazakhstan Academy of Preventive Medicine COPD Center.A history of allergies or hypersensitivity to metal, particularly stainless steel.Any vital sign indicator, such as hypertension or tachycardia at rest that, at the discretion of the investigator, would make participation in the study unsafe or unfeasible.Women who test positive for pregnancy during screening, lactating women, or women planning to become pregnant during the study.Participants using assistive devices like walking aids, as these are likely to interfere with physical activity.Other patients who are considered ineligible for the study by the investigator.

### Sample Size Calculation

The primary endpoints of the study are rates of recruitment, adherence, and retention. To assess the feasibility of the intervention, we plan to recruit 27 participants, which should be enough to get estimates with a sufficient degree of uncertainty. We conservatively predict that 30% of the people invited to participate will be recruited to the study, with a 95% CI of 13-47%. We also assume the dropout rate will be 15%. The accuracy of the estimated retention rate will be at least ±13%. Further, we believe that 70% of participants will adhere to the use of mHealth devices. In this case, the accuracy of the estimate will be at least 17%. All calculations are based on two-way 95% confidence intervals.

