### Outcome Measures

Safety and tolerability will be evaluated through adverse events (AEs), lung function tests, vital signs, and supportive care medications. Primary measures are defined as rates of recruitment, retention, and adherence as well as safety of the intervention that are common for feasibility studies [40]. Recruitment is defined as the number of potential participants screened for study eligibility versus the number of people who enrolled in the study. Retention is defined as the proportion of participants enrolled who completed the intervention and all study measures. Adherence to the study protocol is determined as the proportion of participants enrolled who had all their mHealth parameters registered every day.

The mHealth devices will be compared to the industry standards. Additionally, a questionnaire will be administered to assess the participants’ perceptions of the mHealth technologies used.

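### The stated 95% CI of 13-47% for the recruitment rate treats the 27 people to be enrolled as the number invited; about 90 invitations are implied, so the interval is about 1.8 times too wide (minor, conservative error)

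*Protocol article*

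**What the plan says.** All references are to the Methods of the protocol article.

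- **Status of the endpoint** (Sample Size Calculation): "The primary endpoints of the study are rates of recruitment, adherence, and retention".
- **Planned size** (same section): "we plan to recruit 27 participants". Study Design confirms that this is the number enrolled and followed: "A total of 27 participants in three cohorts will use the mHealth devices for 90 days", that is, three cohorts of nine.
- **Recruitment assumption and precision** (Sample Size Calculation): "30% of the people invited to participate will be recruited to the study, with a 95% CI of 13-47"%.
- **Retention** (same section): "We also assume the dropout rate will be 15"%, followed by "The accuracy of the estimated retention rate will be at least ±13"%. For adherence the section assumes 70%, with a margin of 17%.
- **Basis** (same section): "All calculations are based on two-way 95% confidence intervals".
- **Definition of the measure** (Outcome Measures): "Recruitment is defined as the number of potential participants screened for study eligibility versus the number of people who enrolled in the study".

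The article does not say how many people will be invited or screened.

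**The concern.** A recruitment rate has the people approached as its denominator and the people enrolled as its numerator. The article fixes the numerator at 27 and assumes a rate of 30%, and together these determine the expected denominator. The published interval does not agree with that denominator. It agrees with a denominator of 27.

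Recruitment is one of the three primary feasibility rates, and the expected precision of those rates is the reason that Sample Size Calculation gives for 27 participants. One of its three precision figures therefore answers a different question from the one posed. The sentence also hides the approach workload that the plan implies, which a feasibility study would normally want to show.

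**Working it through.** **Inputs.** Enrolled: 27 (Sample Size Calculation; Study Design). Recruitment rate: 0.30 of those invited. Retention: 1 − 0.15 = 0.85. Adherence: 0.70. Confidence level: 95%, two-sided, so z = 1.96. The number invited is not stated and is derived in step 3.

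**1. Reproduce the stated interval.** The Wald interval is p ± z·√(p(1 − p)/n). With p = 0.30 and n = 27:

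1.96 × √(0.30 × 0.70 / 27) = 1.96 × 0.0882 = 0.173, giving 12.7-47.3%, which rounds to 13-47%.

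The formula rounds to 13-47% only for n = 27, 28 or 29. At n = 26 it gives 12.4-47.6%, and at n = 30 it gives 13.6-46.4%. Other methods at n = 27 do not match: Wilson gives 16.1-48.9% and exact gives 14.0-50.6%.

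**2. Check that the neighbouring figures use the same n.**

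- Retention: 1.96 × √(0.85 × 0.15 / 27) = 0.1347, stated as 13%.
- Adherence: 1.96 × √(0.70 × 0.30 / 27) = 0.1729, stated as 17%.

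Both fit n = 27. For these two rates 27 is the right denominator, because both are proportions of those enrolled.

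**3. Derive the denominator for recruitment.**

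- If 27 were invited: 27 × 0.30 = 8.1, so about 8 would enrol, not 27.
- To enrol 27 at 30%: 27 / 0.30 = 90 invited.

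**4. Recompute at n = 90.**

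- Wald: 1.96 × √(0.30 × 0.70 / 90) = 1.96 × 0.0483 = 0.0947, giving 20.5-39.5%.
- Wilson for 27/90: 21.5-40.1%. Exact: 20.8-40.6%.
- Treating 27 as a fixed enrolment target (inverse sampling, delta method): 1.96 × 0.30 × √(0.70 / 27) = 0.0947, the same half-width.

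**5. Size of the discrepancy.** 0.1729 / 0.0947 = √(90/27) = 1.83.

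**6. Sensitivity to the assumed rate.** With 27 enrolled, n = 27/p and the Wald half-width becomes 1.96·p·√((1 − p)/27).

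| Rate | Implied number invited | Half-width |
|---|---|---|
| 13% | 27/0.13 ≈ 208 | 4.6 points |
| 30% | 90 | 9.5 points |
| 47% | 27/0.47 ≈ 57 | 12.9 points |

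The expression is largest where p²(1 − p) is largest, at p = 2/3: 1.96 × 0.667 × √(0.333/27) = 1.96 × 0.667 × 0.111 = 0.145. On this formula, no recruitment rate combined with 27 enrolled gives a half-width of 17 points.

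**The case against.** **The error has little consequence.** It runs in the safe direction: actual precision would be better than stated. The number of participants does not change. The article ties no progression threshold, test or power claim to the 13-47% range, and the observed interval will come from the actual counts. The Limitations section describes the study as small, exploratory and a pilot. All of this stands and keeps the point minor. It does not make the printed figure right.

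**The use of n = 27 is inferred.** The article does not say which n went into the recruitment interval. That is true, but only n = 27 to 29 returns the figure under the Wald formula, and the same n reproduces both neighbouring margins. Reading 13-47% as a loose planning range instead is hard to square with the section's statement that all its calculations rest on two-sided 95% confidence intervals.

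**Independent invitations are an assumption.** Recruitment by quota and snowball sampling (Participant Recruitment and Registration) may not behave as a binomial sample. This is fair, and it applies equally to the published interval.

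**A stronger reading that the article does not support.** A reader might infer that the retention and adherence margins are wrong too, because a symmetric interval fits poorly at 85% of 27. They are not errors: 27 is the correct denominator, and 13.47 and 17.29 round to the stated 13 and 17. The lower arm of a Wilson or exact interval is longer, but the Wilson half-widths are close to those stated. For 23/27 the interval is 67.5-94.1%, half-width 13.3 points. For 19/27 it is 51.5-84.1%, half-width 16.3 points. The choice among these methods is commonly left to an analysis plan.

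**Conclusion.** The point holds as a minor arithmetic correction. The interval of 13-47% was almost certainly computed with the number enrolled in place of the number invited. On the article's own 27 and 30%, the expected denominator is about 90, the 95% interval is about 20.5-39.5% (Wald) or 21.5-40.1% (Wilson), and the half-width is about 9.5 points. The stated interval is about 1.8 times too wide.

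This rests on three assumptions: that the 30% refers to people invited, as the sentence says; that 27 is the number enrolled, as Study Design confirms; and that invitations can be treated as independent. The figure of 90 is derived, not stated.

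Two further inferences might tempt a reader. One is that the sample size is inadequate. It is not made so, because the correction improves the expected precision for recruitment and leaves the other two rates untouched. The other is that the final analysis will use the wrong denominator. Nothing in the article shows that. Outcome Measures sets the number screened against the number enrolled, so the larger pool is already part of the definition. What remains open there is the wording: Sample Size Calculation counts people invited, while Outcome Measures counts people screened. Neither can be the 27 enrolled, but the two need not be the same number.

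**What to change.** 1. In Sample Size Calculation, replace the recruitment interval with wording such as: *about 90 people are expected to be invited in order to enrol 27; an observed 30% gives a 95% CI of about 21-40%.* Name the interval method beside the figure (Wald 20.5-39.5%; Wilson 21.5-40.1%).
2. Use the same denominator, invited or screened, in Outcome Measures and Sample Size Calculation. If the number screened is chosen, say that the 30% applies to it, or give a separate assumed rate and recompute from 27 divided by that rate.
3. Optional, and not a correction: give Wilson or exact intervals for retention and adherence. If this is done, use one method for all three rates.

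The cost is two or three sentences. The 27 participants, the visits and the data collection stay as they are.

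**Severity:** minor correction.
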